#### Hypothesis 2B

Due to increased adherence, sleep outcomes will be better at 6-month follow-up in PA-CBTI relative to i-CBTI.

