#### Power considerations

We have powered the study for Hypothesis 1A. Hypotheses 1A tests the outcome (i.e. adherence) related to what makes PA-CBTI unique from traditional CBTI. Given the relatively small sample size of our pilot PA-CBTI data (unpublished), we have benchmarked our power analysis to find a medium effect (Cohen’s f = 0.25) in a 3 × 5 (group × session) multivariate analysis of variance (MANOVA) (five sessions, as there are no adherence data in weeks 1 or 2). With alpha = 0.05 and a two-tailed test, a sample size of 120 (40 per group) provides a power of 0.81 to detect a significant effect. Follow-up comparisons also have adequate power [55].

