#### Statistical tests of hypotheses

##### Aim 1

Hypothesis 1A predicts that individuals under partner-assisted conditions will show greater adherence and lower attrition than those under the individual treatment condition. We will test this with 3 × 5 (group × session) MANOVA. The MANOVA will first test the entire set of adherence variables by constructing a latent variable of adherence and using this as the outcome variable. If significant, we will then examine the univariate results for each specific adherence measure. Significant main effects of group (the hypothesised effect) will be followed by comparing PA-CBTI with each of the other groups. Hypothesis 1B will use the Chi-squared test to test the proportion of participants who complete each treatment, with similar follow-ups.

##### Aim 2

Hypothesis 2A anticipates that greater adherence will relate to better sleep outcomes in PA-CBTI and i-CBTI, but not PA-SMT. Multiple regressions will test the hypothesis, with explanatory variables of group (dummy coded), adherence (in the last week of treatment), and group × adherence interaction. The outcome variable will be diary-derived sleep efficiency in the last week of treatment. The interaction term is the effect of interest. Follow-ups will examine the adherence effect within each group. Hypothesis 2B will be tested with Sobel mediation. We hypothesise that PA-CBTI will show (via sleep diaries) greater mean daily sleep efficiency at post-treatment and 6-month follow-up compared with i-CBTI. This effect will be mediated by adherence at the end of treatment (adherence cannot be measured at follow-up since we will not be prescribing sleep schedules).

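### Hypothesis 2B: the only named test, Sobel mediation, is conservative at 40 per arm and does not test the 6-month sleep difference that the hypothesis also asserts

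*Protocol article*

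**What the plan says.** The hypothesis section of the protocol article words 2B as "Due to increased adherence, sleep outcomes will be better at 6-month follow-up in PA-CBTI relative to i-CBTI". That is a difference between two randomised arms together with an explanation for it.

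Under Statistical tests of hypotheses, Aim 2, the method is "Hypothesis 2B will be tested with Sobel mediation". The same paragraph then restates the arm difference as an expectation, "greater mean daily sleep efficiency at post-treatment and 6-month follow-up compared with i-CBTI", and adds "This effect will be mediated by adherence at the end of treatment".

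The section names a MANOVA for 1A, a chi-squared test for 1B and multiple regression for 2A. For 2B it names Sobel mediation only. Power is claimed for 1A alone: "a sample size of 120 (40 per group) provides a power of 0.81 to detect a significant effect". Aim 2 is labelled secondary.

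**The concern.** There are two separate difficulties.

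**The method.** Sobel divides the estimated product of the two paths (arm to adherence, adherence to sleep) by a standard error and refers the result to a normal distribution. With 40 per arm and modest paths the product is skewed, so the test rejects too rarely and discards power that the same data could give.

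**The target.** 2B has two parts. Mediation speaks to the explanation. The Sobel statistic carries no information on whether the arms differ in sleep overall. It could be significant when PA-CBTI clients sleep no better, or non-significant when they do. The arm contrast is also the part that randomisation protects. The path from adherence to sleep is observational, because adherence is not randomised.

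At stake is whether a statement that 2B was supported would mean what the hypothesis says.

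**Working it through.** **Inputs from the article.** 40 per arm (the 120 are completers); Cohen's f = 0.25 over three groups; "With alpha = 0.05 and a two-tailed test", stated for 1A and assumed here for 2B. **Assumed:** both path sizes, because the article gives none.

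**The plan's own figure.** No power is stated for 2B. The 0.81 for 1A can be approached as a between-group effect over five sessions: λ = f²·N·m / (1 + (m − 1)ρ) = 0.0625 × 120 × 5 / (1 + 4ρ), with 2 and 117 degrees of freedom. At ρ = 0.65, λ = 37.5/3.6 = 10.4 and power is 0.82. At ρ = 0.70, λ = 37.5/3.8 = 9.9 and power is 0.80. So 0.81 needs a between-session correlation of about 0.65 to 0.70, which is not stated. It says nothing about 2B.

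**Arm effect on adherence implied by f = 0.25.** If both partner arms are equal and differ from i-CBTI, d = 0.25 / √(2/9) = 0.53. If the three means are evenly spaced, the extremes differ by d = 0.25 × √6 = 0.61.

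**Step 1: Sobel against alternatives.** Model: M = aX + e and Y = bM + e, unit residual SDs, 40 per arm, full mediation, 1,500 simulated trials per scenario, 1,000 draws per interval. Entries are rejection rates.

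| a | b | Sobel | Monte Carlo | Bootstrap |
|---|---|---|---|---|
| 0.53 | 0 | 0.009 | 0.029 | 0.037 |
| 0 | 0.39 | 0.015 | 0.044 | 0.048 |
| 0.53 | 0.26 | 0.189 | 0.372 | 0.382 |
| 0.53 | 0.39 | 0.404 | 0.602 | 0.599 |
| 0.53 | 0.59 | 0.601 | 0.675 | 0.682 |

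The first two rows are null cases. A repeat run gave Sobel against Monte Carlo power of 0.19 vs 0.39, 0.43 vs 0.61 and 0.58 vs 0.66, and Sobel type I error of 0.006 to 0.019.

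The conservatism depends on path size. With a = 0 and 20,000 trials per scenario, Sobel type I error was 0.016 at b = 0.39, 0.035 at b = 0.59 and 0.046 at b = 1.0.

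**Step 2: a second simulation**, with the adherence–sleep path set as a within-arm correlation r (4,000 data sets per scenario; 400 for the bootstrap). Entries are Sobel / bootstrap power.

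| d | r = 0.3 | r = 0.39 | r = 0.5 |
|---|---|---|---|
| 0.53 | 0.29 / 0.50 | 0.46 / 0.68 | 0.59 / 0.69 |
| 0.61 | 0.38 / 0.58 | 0.59 / 0.75 | 0.72 / 0.79 |
| 0.8 | 0.58 / 0.74 | 0.80 / 0.92 | 0.91 / 0.95 |

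**Step 3: does Sobel track the arm difference?**
- True arm difference of 0.65 SD, none of it through adherence: Sobel rejects in 0% of trials, a t-test in 81%.
- Indirect effect present (d = 0.61, r = 0.5, product 0.305) but cancelled by a direct effect of −0.305: Sobel rejects in 71%, a t-test in 5%.

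**Step 4: power of the missing arm comparison if mediation is complete.** Standardised difference D = ab / √(1 + b²); z = D√(40/2); power ≈ Φ(z − 1.96) + Φ(−z − 1.96). With a = 0.53:
- b = 0.26: D = 0.138/1.033 = 0.13, z = 0.60, power 0.09.
- b = 0.39: D = 0.207/1.073 = 0.19, z = 0.86, power 0.14.
- b = 0.59: D = 0.313/1.161 = 0.27, z = 1.20, power 0.23.

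A t-test at 40 per arm has power 0.60 at a difference of 0.5 SD and needs about 0.63 SD for 80%.

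**The case against.** A reader might infer that the plan never tests 2B. The article does not support that. 2B opens with the adherence explanation, and mediation is the right kind of analysis for it. The analysis section also specifies the arm contrast by comparator, outcome and time points, and a mediation analysis usually estimates the total effect along the way. What stands is narrower: no test of that contrast is named, and the Sobel statistic does not supply one. Nor does another named analysis. The 2A regression uses last-week sleep efficiency and makes the interaction the effect of interest, and none of the exploratory examples is this comparison.

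A reader might also infer that 2B is badly underpowered because of Sobel. That too goes beyond the document. Power is claimed only for 1A, Aim 2 is secondary, and the path sizes are assumed. With large paths Sobel reaches 0.80 to 0.91. At medium paths the bootstrap also stays below 0.80, so much of the shortfall comes from sample size.

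Nor is the type I error always far below 5%: it approaches nominal when one path is large.

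Finally, putting the arm comparison first would not rescue a mediated effect. Under complete mediation it is weaker than Sobel (0.14 against 0.40 at b = 0.39). This objection stands and shapes the fix.

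Fewer than 40 per arm at follow-up would lower every figure. But the 120 already counts completers (120/0.8 = 150 randomised, 50 per arm), and follow-up continues for those who stop treatment but stay in the study. A smaller number would be a further assumption, so none is used here.

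**Conclusion.** The point holds in this limited form. Sobel is the only test named for 2B. At 40 per arm with small to moderate paths its type I error is about 0.01 to 0.02 where one path is zero, and it gives up roughly 7 to 20 points of power to an interval method on the same data. The power gap narrows to 4 points at d = 0.8 and r = 0.5. It addresses one half of 2B, and the randomised 6-month contrast, "sleep outcomes will be better at 6-month follow-up in PA-CBTI relative to i-CBTI", has no named test. The mismatch in target does not depend on path sizes. The power and error figures do, and they also assume a two-sided 5% level and normal residuals. Because Aim 2 is secondary, this should be corrected but does not threaten the primary analysis.

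**What to change.** Make two changes to the wording for 2B.

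1. Replace Sobel with a percentile-bootstrap or Monte Carlo 95% confidence interval for the indirect effect.
2. Name a separate PA-CBTI versus i-CBTI comparison of 6-month diary sleep efficiency, adjusted for clinician and sex (the factors used in randomisation) and for the week 1–2 diary value. State that this diary value is collected after randomisation and after the first session, as the Limitations section describes.

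Report the two side by side. Do not make the arm difference a gate for the mediation analysis. Claim 2B in full only if both support it; otherwise say which half was supported.

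The cost is analysis-plan wording and routine software, with no new data. The downside is that the arm comparison has power of only about 0.09 to 0.23 if the effect runs wholly through adherence at the path sizes above. A null result there should be read through its confidence interval and not as evidence of no difference.

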##### Exploratory analyses

Any large study such as this produces a plethora of data useful for analyses not included in the primary and secondary aims. This study is no exception. Examples of such possible analyses from this protocol include: a) the impact of the sleep interventions on sleep in the partner, particularly that subset of partners who show clinically relevant sleep symptoms at baseline; b) dyadic analyses of sleep examining how each individual in the couple affects the other’s sleep and whether this changes with treatment; c) impact of the interventions on relationship satisfaction, mental health symptoms, and quality of life; and d) impact of sleep interventions on objective measures of sleep as assessed via actigraphy.

#### Publications

All results will be published. Trial results will be communicated to participants via email. Publications will be written by members of the research team. Publications are planned corresponding to the main hypotheses and aims of the study: (a) to examine the impact of including the partner in treatment on variables of adherence and completion; and (b) to examine the impact of adherence on insomnia symptoms in the short- and long-term (6 months post-treatment completion). In addition, publications will derive from analyses of secondary outcome variables of interest, such as the impact on relationship satisfaction and mental health.

## Discussion

This is the first randomised clinical trial to investigate the impact of including the bed partner in insomnia treatment. Given that insomnia is a prevalent and costly sleep disorder associated with poor mental and physical health outcomes and an increased risk of accidents, finding the most effective long-term treatment for insomnia is critical. This trial may optimise treatment outcomes for insomnia by improving adherence and reducing attrition. In addition, results will provide insight into the role partners play in clients’ insomnia presentation and help us better understand the impact of the partner on both treatment response and adherence in CBTI. Results could lead to the dissemination of a new intervention readily implementable in a wide range of clinics.

Overall, if our hypotheses are borne out and the partner-assisted version of CBTI improves adherence, and thus sleep outcomes, translation of PA-CBTI into clinics could have positive impacts beyond just sleep. Improvements in insomnia can have positive impacts on psychological health such as depression [56, 57] and anxiety [58]. Given the direct and indirect economic costs of insomnia, this study also holds potential to reduce overall healthcare costs and reduce one source of drag on economic output. It was estimated that in 2016–2017 the impact of inadequate sleep in Australia (population 24.8 million) was $45.21 billion [3].

### Limitations

A limitation of the current study is that neither clients nor clinicians are blinded to the treatment condition, a problem inherent to any intervention of psychotherapy. However, clients are blinded to the study hypotheses and staff who score polysomnography, actigraphy, and questionnaires are blind to treatment condition.

In addition, because we want to be reflective of a clinic-based population, and for the sake of feasibility and to reduce participant burden, the ‘baseline’ sleep diary and actigraphy data are collected between weeks 1–2 of treatment. Hence, this may not be considered as a true baseline. However, between weeks 1–2 the active intervention has not yet commenced as the first session consists of education only. Similarly, our ‘post-treatment’ sleep diary and actigraphy data are collected between weeks 6–7 of treatment. However, the final treatment session is a summary session only and no additional treatment strategies are introduced. All other post-treatment data (e.g. questionnaires) are collected after completion of treatment session 7.

We do not conduct a diagnostic assessment in the partners. Thus, it is possible some of them meet the criteria for a sleep disorder. While we considered conducting such screens, conceptually we do not believe the presence of a sleep disorder should have an impact on the partner’s ability to perform the role defined for them within the intervention. We do, however, have the STOP-Bang from screening, as well as Insomnia Severity Index, sleep diary, and actigraphy at each assessment time point. Thus, we can assess the risk of obstructive sleep apnoea and track symptoms of insomnia in the partners. If we have a couple where both partners report insomnia upon initial contact with the research team, we ask the couple to decide who will enrol as the “client” and who will enrol as the “partner.” While the partner is not required to adopt treatment recommendations themselves, they are welcome to change their behaviour in accordance with treatment if they so desire. This is true whether or not the partner reports sleep problems. Not having formal diagnostic information on the partners limits our ability to assess effectiveness of the interventions in couples where both individuals experience a diagnosed sleep disorder.

Finally, our lack of an individual SMT treatment condition could be considered a limitation of this trial. However, the decision not to include this group was made due to feasibility. An individual SMT group would have required a significantly larger sample allocated to a condition for which we do not expect to have favourable outcomes.

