### Study intervention

Following pre-treatment assessments, couples are randomised to one of three interventions: PA-CBTI, i-CBTI, or PA-SMT. All three interventions consist of seven weekly, 1-h sessions. Participants can discontinue the treatment or the study at any stage. If one of the members of the couples wishes to withdraw, they must withdraw as a couple. Post-treatment and 6-month follow-up data will be collected for those who discontinue the treatment unless they withdraw from the study.

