#### Cognitive behavioural therapy for insomnia (CBTI) and partner-assisted CBTI (PA-CBTI)

We employ a CBTI protocol based on those recommended by the leading experts in the field [40, 41]. This protocol covers the four-factor model of insomnia, sleep restriction, stimulus control, sleep hygiene, stress and relaxation, cognitions and sleep, and relapse prevention. PA-CBTI follows the same session outline as CBTI. The “partner-assisted” aspect involves: (a) teaching the partner all of the same concepts and psychoeducation as provided to the client; (b) providing handouts of session material tailored specifically for the partner; (b) actively engaging the partner in all treatment-related decision making and problem-solving; and (d) actively engaging the partner in determining how they can assist the client to implement treatment recommendations at home and assigning those behaviours as the partner’s homework. For example, we engage the partner along with the client in reviewing sleep diaries of the client, identifying patterns, deciding on changes to make, and determining whether/how to titrate time-in-bed for the coming week. The partner also actively assists the client to pick bed/wake times, activities and locations related to stimulus control principles, and strategies for staying awake and/or avoiding naps, etc. In essence, anything a client does in traditional CBTI is done with input from the partner in PA-CBTI. The therapist emphasises empowerment of the partner to provide support and structure for the client at home to maximise adherence to the intervention.

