#### Partner-assisted sleep management therapy (PA-SMT)

Sleep management therapy includes all aspects of CBTI, except sleep restriction therapy and stimulus control: the 3P model of insomnia, sleep hygiene, stress and relaxation, cognitions and sleep, and relapse prevention. We use the 3P model in PA-SMT because it does not include conditioned arousal as the fourth factor, as this factor is intimately tied to stimulus control. While the primary goal of this study is to compare PA-CBTI with i-CBTI regarding adherence and attrition, inclusion of a non-active control arm facilitates interpretation of results. Specifically, PA-SMT will help control for the interaction of non-specific therapy factors and the involvement of the partner. We expect this condition to show high adherence without conferring benefits to sleep. This is also a valuable control because sleep hygiene (the core of SMT) is the only treatment many individuals with insomnia are offered given that CBTI is typically is only available in specialty clinics. If results indicate that adding the partner increases adherence (as expected) and this, in turn, increases sleep outcomes, PA-SMT would be a much more cost effective way of treating sleep problems than i-CBTI or PA-CBTI. To be clear, we do not expect that outcome, but it would be remiss not to examine for it. In PA-SMT, a different topic is covered in each session, including education about sleep-wake cycle, sleep hygiene, exercise, diet, alcohol, and caffeine. Sleep restriction and stimulus control principles are strictly avoided. Prior studies have shown that SMT is a credible and well-accepted intervention, though it does not improve sleep [43, 43].

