#### Secondary outcome measures

##### Sleep measures

The Insomnia Severity Index (ISI) consists of seven items assessing severity of insomnia in the past week [46, 47].

Using the sleep diary, diary-calculated sleep efficiency, time spent awake after sleep onset, sleep onset latency, and early morning awakenings are secondary outcome variables. These variables are calculated both as weekly averages and as night-to-night variability measures.

Actigraphy, an objective measure, is not part of the diagnostic criteria for insomnia. However, these data are commonly reported in insomnia studies and will provide data for secondary analyses. Participants wear the Actiwatch Spectrum Pro (Philips Respironics) either throughout treatment as well as for 1 week prior to the 6-month follow-up (clients) or for 1 week at each assessment time point (partners). Actiwatch data are collected in 30-s epochs in its standard sensitivity wake threshold (score wake at more than 40 activity counts per epoch) and scored using the Cole-Kripke algorithm. Weekly averages are calculated.

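### The diary and actigraphy 'baseline' is taken after randomisation and after session 1, and the education-only defence fits badly with the definition of the partner-assisted component; the stated hypothesis tests do not use this value, but change or baseline-adjusted analyses should not either

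*Protocol article*

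**What the plan says.** The order of events is clear. Under Study intervention: "Following pre-treatment assessments, couples are randomised to one of three interventions". Under Limitations, the baseline "sleep diary and actigraphy data are collected between weeks 1–2 of treatment". The Sleep measures section has clients wear the device during treatment and again before the 6-month follow-up; no week before randomisation is described.

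The Limitations section discloses the problem: "Hence, this may not be considered as a true baseline". It then answers its own concession by saying that "between weeks 1–2 the active intervention has not yet commenced as the first session consists of education only".

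The section on CBTI and PA-CBTI lists, as element (a) of the partner-assisted aspect, "teaching the partner all of the same concepts and psychoeducation as provided to the client". For the control arm, the PA-SMT section says: "In PA-SMT, a different topic is covered in each session, including education about sleep-wake cycle, sleep hygiene".

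A severity measure is available from before randomisation. "The Insomnia Severity Index (ISI) consists of seven items assessing severity of insomnia in the past week", and the Screening and eligibility and Primary outcome measures sections place the self-report measures in the pre-treatment assessment. The Limitations section also says that partners have the ISI at each assessment time point.

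**The concern.** A baseline for comparing arms should be fixed before the arms can differ. Here couples have been randomised, know their arm (the Blinding section says participants cannot be blinded), and have attended one session before the value is recorded.

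The education-only argument would hold if education were the same in all arms or were not part of what is being tested. By the article's own definition, educating the partner is part of what separates PA-CBTI from i-CBTI. The Background gives a mechanism as well: well-meant accommodation by partners can perpetuate insomnia, which is why they are to be educated. If the partner has been taught by the end of session 1 in the partner-assisted arms and not in i-CBTI, the value may already carry some of the partner effect.

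Any analysis that subtracts this value, adjusts for it, or uses it to define a subgroup would then condition on something treatment may have changed. The candidates are the secondary diary and actigraphy outcomes and the Exploratory analyses, notably partner sleep in those with relevant symptoms at baseline. Partner sleep is the most exposed, because the Limitations section lets partners change their own behaviour in line with treatment.

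**Working it through.** The article states no figure on this point, so there is none to reproduce. The check has three parts.

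**1. Which stated tests use the weeks 1–2 value?** From Statistical tests of hypotheses and Sleep diaries:

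- 1A: adherence measured in sessions 3–7. Not used.
- 1B: proportion completing treatment. Not used.
- 2A: last-week diary sleep efficiency regressed on group, last-week adherence and their interaction. No baseline term and no change score.
- 2B: mean sleep efficiency at post-treatment and 6 months, PA-CBTI against i-CBTI, with mediation by end-of-treatment adherence. No baseline term and no change score.

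None of the four depends on it.

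**2. What would happen if it were used?** Let the true end-of-treatment difference be d, the early between-arm shift already present in the weeks 1–2 value be e (same direction as d), and the correlation between the two measurements be r, with equal SDs and everything in SD units. The expected estimates are:

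- post-treatment value only: d, with SD 1
- change score: d − e, with SD √(2 − 2r)
- adjusted for the weeks 1–2 value: d − r·e, with residual SD √(1 − r²)

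The article gives no d, e or r, so these are assumptions: d = 0.5, r = 0.5, with 40 per arm and two-sided alpha 0.05 (both from Power considerations). For e = 0.2:

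- change: 0.5 − 0.2 = 0.30, power 0.27
- adjusted: 0.5 − 0.5 × 0.2 = 0.40, power 0.54
- post only: 0.50, power 0.61

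For e = 0, all three estimate 0.50, with power 0.61, 0.73 and 0.61 respectively. Over e = 0.1 to 0.3 and r = 0.3 to 0.7, the change score is too small by 0.1 to 0.3 SD. The adjusted estimate is too small by 0.3 × 0.1 = 0.03 up to 0.7 × 0.3 = 0.21 SD. The post-only estimate does not move.

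**3. What would a valid baseline covariate add?** Adjusting for a pre-randomisation score that correlates r with the outcome multiplies the residual variance by 1 − r². The equivalent sample gain is 1/(1 − r²) − 1. The correlation between client ISI and later sleep efficiency is not stated, so a range is shown:

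- r = 0.1: 1/0.99 − 1 = 1.0%
- r = 0.2: 1/0.96 − 1 = 4.2%
- r = 0.3: 1/0.91 − 1 = 9.9%
- r = 0.4: 1/0.84 − 1 = 19.0%

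**The case against.** The strongest reply is that no stated test relies on this baseline. A reader might infer that the Hypothesis 2B arm comparison is biased, because the sleep analyses have no other diary baseline. The article does not support that: 2B compares post-treatment and 6-month values between randomised arms, and such a comparison is unaffected by what happened to an unused earlier measurement. The primary adherence and completion outcomes and the power calculation are equally untouched. This stands in full.

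Second, the article discloses the limitation and gives feasibility and participant burden as reasons. That also stands; only the argument that follows the disclosure is open to challenge.

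Third, a reader might conclude that the value cannot serve as a baseline at all. That goes too far. Bias needs session 1 to have shifted sleep differently between arms within about a week. The Sleep diaries section says changes to sleep begin at session 2, and 'active' can be read as meaning sleep restriction and stimulus control, which the Background names as the strongest components. The article does not assign partner teaching to a particular session and does not describe the first PA-SMT session. A differential effect is therefore plausible but not shown. The reply is incomplete, though: the session 2 statement does not settle what a newly educated partner does at home.

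Fourth, a condensed article need not name its covariates, and leaving one out does not make a randomised comparison wrong. This is right, so the ISI adjustment is offered as an improvement rather than as the repair of an error. Its gain may be small, since every client must have insomnia disorder and the ISI range may be narrow.

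**Conclusion.** The point holds as a matter of labelling and of use in secondary analyses. The weeks 1–2 diary and actigraphy are post-randomisation, post-session-1 measurements, and the reason given for treating them as untouched by treatment conflicts with the article's own account of the partner-assisted component. That the partner is taught in session 1, and that this applies to PA-SMT, is an inference from the arms' design.

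The four hypothesis tests as written are not biased. The exposure is conditional on two things: that a secondary or exploratory analysis uses the value as a reference, covariate or subgroup definer, and that session 1 acts differently by arm. If both hold, the assumed shifts above pull an estimate towards zero by 0.03 to 0.3 SD, depending on method. If session 1 has no differential effect by week 2, there is no bias. All of these sizes rest on assumed inputs.

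**What to change.** - Label the weeks 1–2 diary and actigraphy as the first post-randomisation measurement and report it by arm. Do not use it as change reference, adjustment covariate or definer of a baseline subgroup for between-arm effects.
- Define the symptomatic-partner subset in Exploratory analyses from the partner ISI taken before randomisation.
- Add the pre-randomisation client ISI as a covariate in the Hypothesis 2B models, both the arm comparison and the adherence–outcome path, and in the secondary sleep outcome models. It cannot bias the randomised comparison, and it can reduce confounding by severity on the adherence path, which is not randomised.
- Qualify the Limitations sentence: session 1 precedes the prescribed sleep changes, but partner education is itself part of the partner-assisted component and may have begun.

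The cost is a wording change and one covariate already collected, with no added visit or burden. The assessment schedule in Table 2 is not shown, so the ISI timing should be confirmed against it.
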